## Methods/design

### Study design

The HUMMER trial will follow a multicenter, prospective observational trial design. Approximately 30 hospitals in The Netherlands will participate.

The decision to provide operative or non-operative treatment will be left to the discretion of the attending physician. We chose an observational design because a randomized controlled trial (RCT) would currently not be feasible. Many surgeons prefer not to participate in trials that involve randomization [21] and we know from experience that patients easily refuse to be randomized between operative and non-operative treatment. Inclusion problems were the main reason for failure of a previous RCT with the same research question as this study [20]. Well-designed and adequately reported observational studies are good alternatives to RCTs [22,23]. Preference of observational studies over RCTs in orthopedic trauma has been acknowledged [24,25]. They lead to similar outcomes without the limitations of randomization which may in practice decrease the validity of the outcomes [26,27]. These designs are increasingly used and accepted in surgical studies [28]. In order to answer our research question, we will make adjustments in the statistical analysis by using the propensity matching score method [29-32].

The trial is registered at the Netherlands Trial Register (NTR3617).

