### Study procedures

Clinical evaluation will occur at two weeks (7–21 days window), six weeks (4–8 weeks window), three months (11–15 weeks window), six months (6–7 months window), and 12 months (12–14 months window) after start of treatment [Table 1]. These visits are standard of care for the targeted patient group. At each follow-up visit, the research coordinator or research assistant will ascertain patient status (*i.e.*, adverse events/complications, secondary interventions, etcetera, and will verify information within medical records).

**Table 1 T1:** Schedule of events

**Radiographs & events**	**Screening**	**Enrolment**	**Baseline**	**Post**	**2 weeks**	**6 weeks**	**3 months**	**6 months**	**12 months**
				**surgery**	**(7–21 d)**	**(4–8 we)**	**(11–15 we)**	**(6–7 mo)**	**12-14 mo)**
X-ray	X						X^1^	X^1^	X^1^
Screening	X								
Informed consent		X							
Baseline data			X						
Surgical report form				X					
DASH					X	X	X	X	X
Pain (VAS)					X	X	X	X	X
SF-36					X	X	X	X	X
EQ-5D					X	X	X	X	X
Clinic FU					X	X	X	X	X
Range of motion					X	X	X	X	X
Secondary interventions					X	X	X	X	X
Complications					X	X	X	X	X
Health care consumption					X	X	X	X	X
ADL/work resumption					X	X	X	X	X
Physical therapy					X	X	X	X	X
Constant score						X	X	X	X
Early withdrawal					*	*	*	*	*

^1^X-rays will be taken according to local protocol; all X-rays after three months will be analyzed. The six-month X-ray is needed for assessing fracture healing. If no signs of healing are seen at six months, the 12-month X-ray is also required.

*Only at time of withdrawal.

At each follow-up visit, the range of motion of the shoulder and elbow will be measured using a goniometer by a physician or research assistant. In addition, patients will be asked to complete the questionnaires relating to disability (DASH score including optional modules), pain (VAS), health-related quality of life (SF-36, EQ-5D), health care consumption and production loss. From six weeks onwards, the research coordinator or research assistant will determine the Constant score.

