### Sample size calculation

Calculation of the required sample size for the primary analysis is based on the assumption that the mean DASH in the non-operative group will be 16, with a Standard Deviation (SD) of 16 [8]. We expect less disability (*i.e.*, lower DASH score) at three months in the operative group; the expected DASH score in the operative group will be 10 (SD 10) [8]. A two-sided test with an α level of 0.05 and a β level of 0.2 requires 78 patients in every group. In order to account for loss of patients due to mortality (10%) and loss-to-FU (10% anticipated based upon previous studies by the research team), a sample size of 95 patients per group is needed.

Results of a retrospective study assessing clinical outcome of humeral shaft fractures, showed that 45-55% of all AO-subclasses were treated operatively [18]. In order to assess whether functional outcome scores differ between the fracture subtypes, a minimum of 2x20 patients per fracture subtype is sufficient. In order to achieve that, we need to include until at least 200 patients in both the operative groups and the non-operative group.

For the secondary analysis, some patients may be lost during the propensity score matching. Although we do not have a-priori data to determine how many patients will be lost, the 400 targeted patients will be more than sufficient.

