### Statistical analysis

Data will be analyzed using the Statistical Package for the Social Sciences (SPSS) version 21 or higher (SPSS, Chicago, Ill., USA) and will be reported following the STrengthening the Reporting of OBservational studies in Epidemiology (STROBE) guidelines. Normality of continuous data will be assessed by inspecting the frequency distributions (histograms), and homogeneity of variances will be tested using the Levene’s test.

Descriptive analysis will be performed to report baseline characteristics (intrinsic variables and injury-related variables) and outcome measures for both treatment groups.

For continuous data mean and SD (parametric data) or medians and percentiles (non-parametric data) will be calculated and reported. For categorical data, numbers and frequencies will be calculated and reported for both treatment groups.

Univariate analysis will be performed in order to test the difference in the primary and secondary outcome measures between the operative and the non-operative group. Continuous data such as the DASH score at the different time points (primary outcome) will be tested using a Student’s T-test (parametric data) or a Mann Whitney U-test (non-parametric data). Chi-square analysis will be used for statistical testing of categorical data such as the nonunion rate. A p-value <0.05 will be taken as threshold of statistical significance.

For the primary analysis, a mixed linear regression model will be developed in order to model the relation between different covariates and the DASH score over time. Intrinsic and fracture-related variables that display a p-value <0.5 in univariate analyses will be added as covariate. Similar models will be developed for the Constant, SF-36, and EQ-5D score. Subgroup analysis (*e.g.*, elderly versus <65 years) will be performed.

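### The sample size rests on DASH at three months, but the analysis section never says which treatment result, at which visit, decides the trial

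*Protocol article*

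**What the plan says.** All references are to the Protocol article.

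- **Sample size calculation.** The calculation is introduced as serving the primary analysis. It assumes that "the mean DASH in the non-operative group will be 16, with a Standard Deviation (SD) of 16" and expects a lower score "at three months in the operative group; the expected DASH score in the operative group will be 10 (SD 10". It concludes: "A two-sided test with an α level of 0.05 and a β level of 0.2 requires 78 patients in every group".
- **Statistical analysis, univariate paragraph.** "Continuous data such as the DASH score at the different time points (primary outcome) will be tested" with a t-test or Mann-Whitney test. The same paragraph adds: "A p-value <0.05 will be taken as threshold of statistical significance". It gives no rule for combining or ranking the visits.
- **Statistical analysis, next paragraph.** "For the primary analysis, a mixed linear regression model will be developed", relating covariates to DASH over time. Neither a visit nor a treatment term is singled out.
- **Study procedures and Table 1.** DASH is collected at two weeks, six weeks and three months, and then at "six months (6–7 months window), and 12 months (12–14 months window) after start of treatment": five occasions in all.
- **Study design.** To answer the research question, "we will make adjustments in the statistical analysis by using the propensity matching score method". The Sample size calculation and Statistical analysis sections treat matching as the secondary analysis.
- **Abstract, Background and Outcome measures.** The hypothesis is faster recovery and the primary measure is DASH. None of these sections gives a time point.

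**The concern.** The word primary is attached to three things that are not the same: one visit (in the sizing), every visit (in the univariate paragraph) and a longitudinal model (in the primary analysis). The hypothesis is about speed of recovery, so the treatment difference may well vary between two weeks and 12 months. An average difference over follow-up, a treatment-by-time interaction and a three-month difference are then different quantities and could lead to different conclusions.

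Two things are at stake. First, the two-sided 5% error and 80% power describe a three-month comparison that the analysis section never mentions, so a reader of the results could not tell which p-value they apply to. Second, the text leaves room for a claim resting on whichever visit is significant, including visit-wise tests with no adjustment. In this study the surgeon chooses the treatment, and the Background reports that surgeons say patient characteristics and expected physical demands guide that choice.

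**Working it through.** **1. Reproduce the stated sample size.** Inputs from Sample size calculation: means 16 and 10 (difference 6), SDs 16 and 10, two-sided alpha 0.05, power 0.80.

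n per group = (1.960 + 0.842)² × (16² + 10²) / 6² = 7.849 × 356 / 36 = 77.6, rounded up to 78.

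This matches the protocol. The figure is correct, but it is the size for one two-group comparison at one visit.

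**2. Set the primary labels side by side.**

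| Section | What is called primary | Visit | Adjusted for covariates? |
|---|---|---|---|
| Sample size calculation | Primary analysis: difference in mean DASH | Three months | No adjustment in the formula |
| Statistical analysis, univariate paragraph | Primary outcome: DASH tested visit by visit | All five | No |
| Statistical analysis, next paragraph | Primary analysis: mixed model | Over time, none singled out | Yes |

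Only the first row has a stated power, and neither of the other two rows singles out its visit.

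**3. What the visit-wise tests could do to the error rate.** Inputs: five DASH visits (Study procedures, Table 1) and 0.05 per test (Statistical analysis). Two further inputs are assumptions that the protocol does not give: that any one significant visit counts as success, and the correlation of the test statistics between visits.

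- Independent tests: 1 − 0.95⁵ = 0.226.
- Correlated tests: the probability that at least one of five standard normal statistics exceeds 1.96 in absolute value, from 2 million simulated draws.

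| Assumed correlation | Exchangeable | AR(1) |
|---|---|---|
| 0.3 | 20.9% | 21.8% |
| 0.5 | 18.3% | 20.1% |
| 0.7 | 14.8% | 17.1% |
| 0.8 | 12.7% | 14.9% |
| 0.9 | 10.2% | 11.9% |

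Over correlations from 0 to 0.9 and both structures, the range is about 10% to 23%. These figures cover multiplicity only. They include nothing for confounding.

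**4. What happens once one result is named.** With a single three-month contrast at 0.05, the nominal error is 5% and the required number stays at 78 per group. The plan enrols 200 per group. After a combined 20% loss, 160 are evaluable: standard error = √(356/160) = 1.49, 6/1.49 = 4.02, and 4.02 − 1.96 = 2.06, which gives power of about 98%.

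If all five visits were kept confirmatory at 0.05/5 = 0.01 each, n = (2.576 + 0.842)² × 356/36 = 115.5, so 116 per group, or 116/0.8 = 145 after 20% loss. Power at three months with 160 evaluable per group would be about 93%.

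Both options fit within 400 patients. The power figures use the protocol's own means and SDs for an unadjusted comparison. Adjustment for covariates that predict treatment could lower them somewhat.

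**The case against.** The strongest reply is that the protocol does have a hierarchy. It names the mixed model as the primary analysis and matching as secondary, and it places the visit-wise tests under univariate analysis, where all outcomes are tested. On that reading the bracketed label merely says that DASH is the primary measure. Model terms and visit coding are commonly left to an analysis plan, and a longitudinal model suits a hypothesis of faster recovery. Sizing on one visit does not by itself make that visit the sole endpoint.

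Much of this stands, and it rules out three stronger readings that a reader might infer:

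- **That the plan's false-positive rate is 13-21%.** The documents do not support this as a property of the plan. It needs an any-visit success rule and between-visit correlations, and neither is in the text. If one prespecified mixed-model contrast decided the trial, the nominal rate would be 5%.
- **That there are many rival primary analyses of equal rank.** The text calls one model primary, so a bare count of candidates ignores its ordering.
- **That Study design makes matching the primary analysis.** It says matching will be used to answer the question, which a secondary analysis can also do. The wording is loose and needs aligning, but it is not a second primary analysis.

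The reply does not remove the mismatch. The same document sizes its primary analysis at three months, defines that analysis over all visits, and attaches the primary label to unadjusted tests at each visit. That is a disagreement in what is written, not a detail held over. If an unseen analysis plan already names the contrast, the article still has to be brought into line with it.

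**Conclusion.** The point holds as an inconsistency. The stated two-sided 5% error and 80% power belong to a three-month comparison that the Statistical analysis section never identifies as decisive, and the named primary model has no specified deciding treatment result. The sample size arithmetic is sound and enrolment is ample.

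The multiplicity risk is conditional. If any significant visit among five were accepted as success, the chance of at least one false positive would be up to about 23%, and roughly 13-21% at an assumed exchangeable correlation of 0.8 down to 0.3. Any bias in the unadjusted tests would be additional and cannot be sized from the documents. Because the gap concerns the result on which the main conclusion rests, it should be closed before the data are analysed.

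**What to change.** In Statistical analysis, name a single primary result: the covariate-adjusted operative minus non-operative difference in DASH at three months, estimated from the mixed model with visit as a category and a treatment-by-visit term, tested two-sided at 0.05. This agrees with the existing Sample size calculation. Then:

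- make the other visits and the overall time course secondary;
- state that the unadjusted visit-wise t and Mann-Whitney tests are descriptive;
- keep the propensity-matched analysis as the secondary or sensitivity estimate of the same three-month contrast, and reword Study design to say so.

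An overall treatment effect or a treatment-by-time test would also be defensible given the hypothesis, but the sample size justification would then have to be rewritten for it. The three-month contrast is the choice that needs no such change.

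The cost is small: no extra patients, visits or measurements. The downside is that significance at other visits becomes secondary evidence. The Discussion section reports that inclusion began in October 2012, so the change fixes the deciding result in a running study and must be a dated amendment made before analysis.

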The best type of treatment is still debated. Surgeons state that their experience, patient characteristics and expected physical demands in daily living guides treatment decision. In the elderly patients, some surgeons might prefer immobilization while others may primarily operate as they fear inferior functional outcome after non-operative treatment. In younger patients, some surgeons directly perform a surgical intervention while others primarily choose non-operative immobilization, followed by surgical intervention if needed. However, our retrospective study showed an approximately 50% operation rate irrespective of fracture subclass with no obvious differences in patient or fracture characteristics across classes [18]. Since randomized or high-quality comparative observational studies are lacking, a recent Cochrane review concluded there is no evidence of sufficient scientific quality available to inform the decision to operate or not [19]. High-quality clinical studies are thus urgently needed to resolve this clinically relevant problem. RCTs for this injury have shown feasibility issues; one RCT continued as an observational study due to severe recruitment problems [20]. The HUMMER study is designed to provide the best achievable evidence to answer this unresolved problem using an observational trial design.

The primary objective of this study is to examine the effect of operative versus non-operative treatment on the DASH (Disabilities of the Arm, Shoulder, and Hand) score, reflecting functional outcome and pain of the upper extremity, in adult patients who sustained a humeral shaft fracture. Secondary aims are to examine the effect of operative versus non-operative treatment on functional outcome, the level of pain, range of motion of the shoulder and elbow joint, the rate of secondary interventions and complications, the time to resumption of work and activities of daily living, health-related quality of life, costs, and cost-effectiveness in these patients.

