### Outcome measures

The Disabilities of the Arm, Shoulder and Hand (DASH) outcome measure will serve as primary outcome measure. The DASH is a validated 30-item, self-report questionnaire designed to help describe the disability experienced by people with upper-limb disorders and also to monitor changes in symptoms and function over time [34,35]. It is scored in two components: the disability/symptom section (30 items, scored 1–5) and two optional Work and high performance Sport/Music modules (each 4 items, scored 1–5). The DASH disability/symptom score is a summation of the responses to 30 questions on a scale of 1 to 5, with an overall score ranging from 0 (no disability) to 100 (severe disability). At least 27 of the 30 items must be completed for a score to be calculated. The DASH optional modules aim to measure symptoms and function in athletes, performing artists and other workers whose jobs require a high degree of physical performance. These optional models are scored separately and each contains four items, scored 1–5. All items must be completed for a score to be calculated.

The secondary outcome measures are:

• Constant score

• Pain level at both sides (VAS)

• Range of Motion of the shoulder and elbow joint at both sides

• Rate of complications

• Rate of secondary interventions

• Time to resumption of work and other activities of daily living

• Health-related quality of life: SF-36 and EQ-5D

• Radiographic healing

• Cost of health care use and production loss

• Cost-effectiveness

The Constant score reflects both function and pain [36]. This scoring system consists of four variables that are used for assessing shoulder function. The right and left shoulder are assessed separately. The subjective variables are pain (15 points), activities of daily living (ADL; *i.e.*, sleep, work, recreation/sport; 10 points), and arm positioning (10 points), which give a total of 35 points. The objective variables are range of motion (ROM; 40 points) and strength (25 points), which give a total of 65 points. ROM includes forward flexion (10 points), lateral elevation (10 points), external rotation related to the head (10 points) and internal rotation related to the spine column (10 points). ROM will be measured with a goniometer. Strength of abduction will be measured using a calibrated spring balance.

Pain level will be determined using a 10-point Visual Analog Scale (VAS), in which 0 implies no pain and 10 implies the worst possible pain.

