For the secondary analysis we will develop a propensity score model as published before [43,44]. Characteristics including fracture type, age, gender, mechanism of injury, dominance, and activity levels will be included in this model; the resulting propensity score represents the chance of being operated. Next, the logit of the propensity score will be used in order to match each patient receiving operative treatment with one or more patients receiving non-operative treatment. The effect of operative treatment will be analyzed with linear or ordinal logistic mixed effects regression analysis taking the matched-pairs design into account. In the matched cohort, comparisons will be performed using a McNemar test (for categorical data), and a paired sample t test (parametric, continuous data) or a Wilcoxon signed rank test.

The economic evaluation will be performed from a societal perspective. Costs will be measured in accordance with Dutch guidelines for economic evaluations, using standard cost prices as published by Hakkaart-Van Rooijen et al. where possible [45]; effects will be discounted at a rate of 1.5% and costs at 4% per year [45]. The incremental cost-effectiveness ratio (ICER) of operative versus non-operative treatment will be expressed in a cost-utility ratio (*i.e.*, cost per QALY) using the EQ-5D utility score as effect measure. Uncertainty around this ratio will be presented using confidence ellipses on the cost-effectiveness plane and acceptability curves.

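### In the full cohort, non-union, complications and secondary interventions get only an unadjusted chi-square test; their only stated confounding control is the secondary matched analysis

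*Protocol article*

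**What the plan says.** All places are in the protocol article.

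- **Allocation (Study design).** "The decision to provide operative or non-operative treatment will be left to the discretion of the attending physician".
- **Basis of the choice (Background).** "Surgeons state that their experience, patient characteristics and expected physical demands in daily living guides treatment decision".
- **Harm outcomes (Outcome measures).** "Rate of complications" is a listed secondary outcome, and non-union is one of the complications defined there. The rate of secondary interventions is listed next to it.
- **Crude tests (Statistical analysis).** "Univariate analysis will be performed in order to test the difference in the primary and secondary outcome measures between the operative and the non-operative group". For the harms: "Chi-square analysis will be used for statistical testing of categorical data such as the nonunion rate". The significance threshold is p<0.05.
- **Adjusted full-cohort models (same section).** Primary outcome: "a mixed linear regression model will be developed in order to model the relation between different covariates and the DASH score over time", with intrinsic and fracture-related variables as covariates if they pass a univariate screen at p<0.5. Then: "Similar models will be developed for the Constant, SF-36, and EQ-5D score". No harm outcome is on this list.
- **Matched analysis (same section, labelled secondary).** Operated patients are matched on the logit of a propensity score to one or several non-operated patients. "In the matched cohort, comparisons will be performed using a McNemar test (for categorical data". Linear or ordinal logistic mixed models are also planned there, without naming their outcomes.

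**The concern.** With treatment chosen on patient characteristics, a crude difference in harm rates mixes the effect of surgery with the kind of patient who is operated on. Age, smoking, osteoporosis and ASA class, all collected at baseline, could plausibly bear both on the choice and on the risk of non-union or complications. The protocol accepts this logic for four outcome scores by stating adjusted models for them, but states none for the harms in the same cohort. A reader of the full-cohort results would then see an adjusted functional effect beside an unadjusted harm comparison with a significance verdict. Confounding could create a harm difference or hide a real one. Non-union is one of the outcomes on which the Background weighs the two strategies, and the Background itself says that data are lacking to tell which complications are treatment-related.

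**Working it through.** **1. The plan's own figures.** The only sample size is for DASH: means 16 and 10, SDs 16 and 10, two-sided α 0.05, power 80%.

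n per group = (16² + 10²) × (1.960 + 0.842)² / 6² = 77.6, so 78, as stated. Inflation: 78 × 1.1 × 1.1 = 94.4, so 95, as stated. No sample size is given for harms. The target of 200 per group is used below.

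**2. Which analysis covers which outcome.**

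| Outcome | Full cohort, crude | Full cohort, adjusted | Matched cohort (secondary) |
|---|---|---|---|
| DASH | t-test or Mann-Whitney | mixed linear model | paired t-test or Wilcoxon |
| Constant, SF-36, EQ-5D | t-test or Mann-Whitney | similar models | paired t-test or Wilcoxon |
| Non-union, complications, secondary interventions | chi-square | none stated | McNemar |

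The mixed models of the matched analysis are left out of the last column because their outcomes are not named. Only non-union is named for chi-square. Complications and secondary interventions follow because the univariate sentence covers all secondary outcomes.

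**3. How far the crude test could mislead.** The documents give no imbalance between treatment groups, so this is illustration only. Assumptions: no true treatment effect; one binary risk factor; non-union 10% without it; odds ratio 2 or 3 with it; 200 per group.

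- Risk with the factor: odds = OR × 0.10/0.90, giving 0.182 (OR 2) or 0.25 (OR 3).
- Crude rate in a group with prevalence q: q × r₁ + (1 − q) × 0.10. Example, OR 3 and q = 0.30 v 0.50: 0.30 × 0.25 + 0.70 × 0.10 = 14.5%, against 0.50 × 0.25 + 0.50 × 0.10 = 17.5%.
- Rejection probability: Φ((d − 1.96·SE₀)/SE₁) + Φ((−d − 1.96·SE₀)/SE₁), where d is the absolute difference, SE₀ the pooled and SE₁ the unpooled standard error. In the example d = 0.030 and both SEs are about 0.0367, so Φ(−1.14) + Φ(−2.78) ≈ 0.13.

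| Factor present, operated v non-operated | OR 2: crude rates, rejection | OR 3: crude rates, rejection |
|---|---|---|
| 45% v 50% | 13.7% v 14.1%, 5.2% | 16.8% v 17.5%, 5.5% |
| 40% v 50% | 13.3% v 14.1%, 5.7% | 16.0% v 17.5%, 6.9% |
| 30% v 50% | 12.5% v 14.1%, 7.7% | 14.5% v 17.5%, 12.9% |
| 25% v 55% | 12.0% v 14.5%, 11.2% | 13.8% v 18.2%, 23.2% |

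With no imbalance the rate is 5%.

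**4. Is an adjusted harm model feasible?** The Background gives non-union as 15-30% after operative and 2-23% after non-operative treatment. At 200 per group:

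- both lower ends: 200 × (0.15 + 0.02) = 34 events;
- both upper ends: 200 × (0.30 + 0.23) = 106 events.

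At an assumed rule of thumb of 10 events per parameter, that supports about 3 to 10 parameters. A model with treatment and a single propensity-score covariate fits throughout. A long covariate list does not fit at the low end.

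**The case against.** **Confounding control for harms is already planned.** The Study design section names propensity matching as the adjustment for the research question, and the matched cohort includes a test for categorical data. This stands. A reader might infer that harms are never adjusted, or that the benefit-harm balance must set an adjusted DASH effect against a confounded harm rate. The document does not support either inference, since matched DASH and matched harm results would both exist. The matched analysis has limits, though. It is secondary, and the Sample size calculation section says patients may be lost in matching without knowing how many. That loss costs precision and generalisability; it does not by itself show that the matched comparison is confounded. McNemar does not fit sets with several controls. The variables named for the score do not include ASA class, smoking, comorbidity or osteoporosis, although the list is not presented as complete.

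**The crude tests apply to every outcome and are called univariate.** True. The protocol nowhere says that the chi-square carries the harm conclusion. But for harms it is the only full-cohort result stated.

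**This is detail for the full protocol or analysis plan.** The Abstract does mention multivariable analyses in general, and a condensed article need not list every model. Here, however, the article fixes the test for non-union and lists the outcomes to be modelled. The point is about that stated choice.

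**The groups may be similar.** The Background reports about 50% operated irrespective of fracture subclass, with no obvious differences in characteristics across classes, and the Sample size calculation section gives 45-55%. This weakens fracture subclass as a confounder. It does not establish balance between treatment groups on age, smoking or bone quality.

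**Conclusion.** The point holds for the full cohort: the harms have an unadjusted significance test and no stated adjusted model, while DASH, Constant, SF-36 and EQ-5D have one. Because treatment is chosen on patient characteristics, that harm comparison cannot be attributed to treatment. The primary DASH analysis is unaffected.

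The size of the bias is unknown. In the illustration the false-positive rate stays close to nominal (about 5-7%) at 5-10 points of imbalance and reaches 8-23% at 20-30 points. These figures rest on an assumed 10% baseline risk, assumed odds ratios of 2-3 and assumed prevalences. Someone might take the upper figures as a forecast, but nothing in the document shows imbalances that large. This is a point about analysis, not about clinical management.

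**What to change.** In the Statistical analysis section, after the sentence on the Constant, SF-36 and EQ-5D models:

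- Add a full-cohort logistic regression for each of non-union, any complication and any secondary intervention, with treatment plus either a small prespecified set of baseline confounders (for example age, ASA class, smoking and fracture type) or the propensity score as a single covariate. Use penalised likelihood where events are sparse, which may include non-union itself.
- Do not carry over the covariates that passed the p<0.5 screen for DASH. That screen belongs to another outcome and could select more terms than 34 events can support.
- Report the adjusted effect with its 95% CI as the full-cohort harm result, alongside the matched analysis, and label the chi-square results as unadjusted and descriptive.
- In the matched analysis, either confine McNemar to 1:1 pairs or name a method for sets with several controls, such as conditional logistic regression.

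The cost is a few extra models on data already collected. The downside is that adjustment can cover only a few covariates when events are few, so some residual confounding must be acknowledged.
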